### Intervention

The collaborative care intervention includes up to three intervention components, as detailed below: 1) care management, 2) cognitive-behavioral therapy (CBT), and 3) stepped up medication consultation, if warranted. All care management and CBT are delivered by one of two study care managers on the study, both of whom are master’s level trained mental health professionals. Medication consultation is provided by a child psychiatrist on the basis of information provided by the care manager and the supervisory team; however, all prescriptions are ultimately managed by the adolescent’s existing primary care or specialty providers.

The components of the intervention can be delivered through in-person visits, HIPAA compliant video conferencing, or phone call. Zoom Video Conferencing software meets the HIPAA compliant criteria and is used with families that choose to receive the intervention in this manner. At the beginning of the intervention, families are offered this option to meet with the care manager for both care management and CBT sessions. Zoom enables care managers to meet with families that are unable to meet in person regularly. If families choose Zoom, care managers provide directions and support about how to connect by computer or by smartphone/tablet. Connecting by computer requires a camera, microphone, and internet connection. Families will be required to download Zoom software to their computer. Connecting by smartphone/tablet requires an internet connection or the ability to use cellular data. Families are required to download the Zoom application through their app store.

#### Care management

The care manager will call the family to set up an initial meeting focused on eliciting the adolescent’s and family’s concerns and treatment needs and preferences [56, 57]. The care manager will share their study cell phone number and encourage calls for questions and concerns both from the adolescent and parent participants. She will schedule ongoing times to meet the adolescent during the initial days and weeks post-randomization.

Care management meetings with subjects can occur in-person, by HIPAA compliant video conferencing, or phone call. The care manager will elicit information to formulate a comprehensive post-injury treatment plan, integrating the adolescent’s family members whenever feasible and acceptable to the adolescent. Initial discussions between the care manager and the adolescent and family members may also highlight any issues and concerns related to return to sports or academic activity.

The care manager acts as an advocate for the adolescent and family based on their needs and presenting concerns. If the adolescent or family member discloses difficulties related to academics, the care manager will contact and coordinate care with school administration. If previous or new mental health challenges arise, the care manager will support the family in finding an appropriate outside provider. The care manager will reach out to this provider to coordinate and confirm appropriate care. They will also present the plan, issues that occur during the process, and feedback from the family in the weekly intervention team meeting.

Standardized instruments will be used to monitor post-concussive, anxiety, and depressive symptoms at regular post-injury intervals. The intervention includes a motivational interviewing element embedded within care management that targets both treatment engagement and high risk behaviors that threaten recurrent injury. The motivational interviewing intervention element consists of a graded sequence of clinical tasks, including: a) eliciting from adolescents their views of the importance of changing, and of their confidence in being able to change behaviors, b) giving adolescents personalized feedback, and c) clarifying the adolescent’s behavior change goals and action plans.

#### Cognitive-behavioral therapy

The intervention includes modular CBT targeting post-concussive, anxiety, and depressive symptoms. In this CBT treatment, the adolescent is taught coping skills, relaxation strategies, and cognitive strategies to manage their symptoms, while they are encouraged to increase appropriate activation, including pacing of activities. The treatment manual is intentionally flexible to allow for tailoring to the unique presentation and needs of the adolescent, including how many sessions and what specific modules of content to deliver. CBT sessions will be tailored to adolescent preferences and may occur either in-person, by HIPAA compliant video conferencing, or phone call.

The first session involves psychoeducation and goal setting to collaboratively develop an individualized intervention plan and behavioral targets with the adolescent and their parent. Specific CBT intervention elements covered in subsequent modules may include: pain management, problem-solving, behavioral activation, mindfulness, challenging negative thinking, relaxation and imagery, avoidance, emotion regulation, family communication skills, parent and child interaction, sleep hygiene, or brief crisis intervention support. For adolescents who demonstrate adequate CBT readiness/motivation, homework assignments are given [25, 58].

Treatment is delivered primarily in individual sessions with adolescents, although parent involvement in the treatment is strongly encouraged, with the following goals: 1) educating parents about concussion symptom management, 2) creating common goals and a framework for reaching those goals, and 3) understanding the parental role in support and stress processes. The care manager monitors symptoms (depression, anxiety, PCS) on a session-by-session basis using standardized instruments to inform how treatment is working and whether to increase the intensity of CBT or consider a psychiatric consultation regarding medication initiation or changes. Adolescents may discontinue CBT when their symptoms have abated or if they feel that additional sessions are not needed/would not be helpful.

#### Medication consultation

The stepped-up medication consultation aims to initiate and ensure adequate follow-up of psychopharmacological treatment targeting PCS as well as anxiety and depressive symptoms. In the current stepped care protocol, CBT is the first treatment of choice. For patients that do not adequately respond to the combination of CBT and care management, medications become a stepped-up care option particularly when it appears that there are recalcitrant post-concussive, anxiety, or depressive symptoms that would not readily diminish without initiation of pharmacotherapy. Persistent headaches and/or insomnia can also be important treatment targets for medications when problematic and persistent. Patients who enter the intervention arm of the protocol and are already prescribed psychotropic medications will be prioritized for medication consultation.

The stepped care medication consultation option will start with a brief report from the care manager regarding symptom patterns over time; the adolescent’s current injury status; current and past comorbid medical conditions; current primary care, sports medicine and rehabilitation service use; current medication use including analgesics and psychotropic medications; prior psychotropic medication use; and attitudes and beliefs surrounding medication treatment [25, 31, 46].

For adolescent patients who have never received prior treatment for depression or anxiety, a SSRI or newer non-SSRI antidepressant is the treatment of choice [59–65]. Recommendations for medications will be made to the adolescent’s primary care physician and specialty care provider who is managing the concussion. In our prior Care for Post-Concussive Symptoms pilot study, adolescent care providers including pediatricians and treating physicians in rehabilitation medicine were often the primary prescribing providers [36, 46]. If negative side effects are reported by the adolescent, the care manager will tell the family to contact their prescribing physician as soon as possible. The care manager will also bring these concerns to the attention of the study’s child psychiatrist for consultation within 3 days, to seek recommendations for medication change or discontinuation, which will then be conveyed to the prescribing provider. The study team has expertise in the provision of long-distance pharmacological consultation, thus enhancing the reach of the current intervention in comparison to the smaller scale pilot study.

### Usual care for control subjects

Control subjects will receive usual care. Usual post-injury care may include the routine use of sports medicine, rehabilitation medicine, physical therapy, primary care emergency department, and specialty mental health services. Usual care has been selected for controls as it remains the optimal comparator condition for policy guidelines and represents care now being delivered in specialty clinics across the USA. Usual care does include referral to specialty providers caring for adolescents with concussion as needed. All aspects of concomitant care are permitted during the trial following enrollment across study arms. For control group participants who indicate suicidal ideation on follow-up surveys, a clinical assessment is conducted by a study principal investigator by telephone, with appropriate follow-up, discussion with a parent/guardian, and provision of referral resources if needed based on risk assessment.

#### Masking of treatment allocation

Study group assignments will be kept in sequentially numbered opaque envelopes that will be opened by unblinded study staff after baseline assessments to ensure allocation concealment of the randomization group. Research assistants conducting all baseline assessments and follow-up interviews will be blinded to block sizes and remain blinded to study group assignment throughout the study. Since the study team includes both unblinded (principal investigators, study coordinator, care managers) and blinded (research assistants) staff, unblinding of the research assistants is not ever necessary, although it could inadvertently occur through participant disclosure.

#### Data management

Data from the study will be derived from subject responses to questionnaires, school records, and medical records. All data will be collected specifically for research purposes. Individually identifiable private information will be collected from research participants. To ensure subject confidentiality, all research materials will be kept in a locked file cabinet in a badge-only accessible research unit.

All medical record information and other electronic data will be stored on HIPAA-compliant password-protected computers and encrypted. After data are collected, information which would identify the subjects will be removed and code numbers used instead. A study code will be assigned to each subject. All subject data will be linked to the study codes in one master file that will be encrypted and stored on a secure laboratory study computer configured behind the departmental firewall. Study data will be collected and managed using REDCap (Research Electronic Data Capture) electronic data capture tools hosted at the University of Washington [66]. REDCap is a secure, web-based application designed to support data capture for research studies. All data will be stored for 5 years after completion of the study, and only the study team will have access to the data. Additionaly, a bi-annual data quality report is produced (and shared with the DSMB) to assess quality of data collected. During these routine data quality audits, an unblinded research staff assesses missingness of data, performs range checks for data values, and conducts source data verification of electronic data.

### Quality control procedures

#### Training research assistants

During the start-up phase of the protocol, the research assistants will be trained to a reliable standard with the assessment procedures through: 1) attendance of practice training sessions on survey outcome assesment and procedures in accordance with Good Clinical Practice guidelines, and 2) individual supervision and shadowing with lead clinical research staff.

### Baseline measures

Parents will be asked to describe family demographic characteristics including marital status, ethno-cultural heritage, and number of children. Caregivers’ education levels and combined family incomes will also be obtained and used as a measure of family resources. We will collect information on prior history of treatment for psychiatric disorder, prior and current use of psychotropic medications, prior PCS, and use of other healthcare services both by means of parent questionnaire and medical record review [25, 67].

### Outcome evaluation

For all adolescents enrolled in the trial, follow-up surveys will be completed online or by telephone at 3, 6, and 12 months after the traumatic injury, with monetary incentives for each. Participants will be invited to complete follow-up surveys even if they have discontinued or not fully engaged in the intervention protocols. Research assistants will be trained to bring up specific discussion points about the benefits of study participation in cases where control group families are unsure about continuing their participation, to increase their retention and counteract differential dropout. Table 1 provides a summary of data collection time points. The study includes a variety of outcome measures to cover the wide gamut of issues experienced by youth with persistent post-concussive symptoms, such as depression, anxiety, sleep interference, headaches, and poor school performance.

**Table 1 Tab1:** List of study measures by timepoint

Construct	Measure	Screen	Base-line	3 months	6 months	12 months
History of TBI		P	P			P
Post-concussive symptoms	HBI	A, P	A, P	A, P	A, P	A, P
Depressive symptoms	PHQ-9		A, P, PS	A, P, PS	A, P, PS	A, P, PS
Anxiety symptoms	Generalized Anxiety Disorder-7 item, revised Child Anxiety and Depression Scale		A, PS	A, PS	A, PS	A, PS
Quality of life	Peds Quality of Life		A, P	A, P	A, P	A, P
Exposure to life stress–adolescent	UCLA Reaction Index Trauma History, at baseline; Life Events Checklist–Child Form at 6 and 12 months		A		A	A
Exposure to life stress–parent	National Comorbidity Study –Trauma History measure at baseline; LES at 6 and 12 months		PS		PS	PS
Sleep	Adolescent Sleep-Wake Scale		A	A	A	A
Headache	TBI-QL–Headache Pain		A	A	A	A
School attendance and performance	Questionnaire and school records		P, SR	P	P	P, SR
Satisfaction with care	Client Satisfaction Questionnaire				A, PS	
Prior psychiatric history	Questionnaire		P			
Demographic characteristics	Questionnaire		PS			
Health Service and Medication Utilization	Questionnaire		P	P	P	P

*A* adolescent, *P* parent report of youth, *PS* parent self-report, *SR* school records, *TBI* traumatic brain injury

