**Methods/design:**

This investigation is a randomized comparative effectiveness trial to receive intervention (collaborative care) or control (usual care). Two hundred sports-injured male and female adolescents aged 11–18 years with three or more post-concussive symptoms that persist for at least 1 month but less than 9 months after injury will be recruited and randomized into the study. The trial focuses on the effects of the intervention on post-concussive, depressive, and anxiety symptoms measured 3, 6, and 12 months after baseline.

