## Methods/design

### Design

This investigation is a randomized comparative effectiveness trial allocated in a 1:1 ratio to receive intervention (collaborative care) or control (usual care). The trial focuses on the effects of the intervention on youth outcomes 3, 6, and 12 months after baseline. Figure 1 shows the intervention model and Fig. 2 shows recruitment and flow of participants through the study.

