### Participants and procedures

#### Eligibility criteria

Two hundred sports-injured male and female adolescents aged 11–18 years with at least three PCS that persist for at least 1 month but less than 9 months after injury will be recruited and randomized into the study if they and a parent can read and speak in English. The diagnosis of concussion will be made by a qualified medical provider. Adolescents with prior concussions will not be excluded. There will be active recruitment by weekly scanning of the appointment lists for the Sports Medicine, Neurology, Neurosurgery, and Rehabilitation Medicine clinics at Seattle Children’s Hospital main campus and four satellite locations, and the Sports Medicine and Rehabilitation Medicine clinics at Harborview Medical Center. Some of these settings serve patients from surrounding states, who will also be eligible for this trial.

Adolescents who have suffered spinal cord or other severe injuries that prevent participation will be excluded from the study. Adolescents will also be excluded if they have had a diagnosis of schizophrenia or psychosis, or present with active and acute suicidal ideation. Parents of adolescents who report concerns about their child’s ability to communicate may be excluded from the study pending consultation with principal investigators.

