##### School performance

Parents will complete the eight-item Concussion Learning Assessement and School Survey to measure post-injury academic experiences, including number of days missed, concerns about school performance, impact on grades, and whether the school provides academic support to kids with concussion [74]. This will be repeated at each of the follow-up assessments. Participants’ 1 year pre- and post-injury school attendance and grades will also be obtained from school records as a measure of academic outcomes [31] and will be re-coded using a standardized four point grade-point average (GPA).

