#### Power analysis and sample size

Power analyses were conducted using PASS software to determine the appropriate number of participants for the study [91–93]. Based in part on prior investigation by the study team, assumptions including four assessment points (baseline, 3 months, 6 months, and 12 months), equal correlations over time of ρ = 0.7, two-tailed alpha = 0.05, and 10% 12-month attrition were used for all power analyses. We used data derived from our prior large scale collaborative care investigations to estimate symptomatic and quality of life treatment effects for power calculations [25, 94]; data from the pilot were used to corroborate treatment effect estimates derived from these larger scale trials [95, 96]. The study team conservatively estimated that the 12-month persistent concussive symptom treatment effect will be d = 0.35–0.40, using preliminary data derived from prior study team large scale collaborative care investigations [25, 31].

To estimate the power to detect a group-by-time interaction effect on persistent concussive symptoms we used the primary continuous HBI total symptom score with baseline mean = 33.0 and common SD = 11.0. The study will require recruitment of 200 subjects (100 subjects in each group) in order to retain 180 subjects at the 12-month post-injury follow-up. With a final sample of 180 subjects, the power to detect a significant group-by-time interaction with a between-group effect size of d = 0.36 on the HBI somatic symptom scale is 0.80.

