## Trial status

The trial began recruitment of participants in March, 2017, and we expect to recruit the full sample near the end of March, 2019. The 12-month follow-up assessments of all the participants would then be completed by March, 2020. Protocol version #7; protocol version date October 26, 2018.

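### The follow-up surveys are dated from injury in some sections and from baseline in others, and the school-record year includes pre-randomization time for every participant

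*Protocol article*

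**What the plan says.** **Baseline clock.** The Design section says: "The trial focuses on the effects of the intervention on youth outcomes 3, 6, and 12 months after baseline". The Methods/design paragraph of the abstract likewise refers to "post-concussive, depressive, and anxiety symptoms measured 3, 6, and 12 months after baseline".

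**Injury clock.** The Outcome evaluation section, which governs data collection, says that "follow-up surveys will be completed online or by telephone at 3, 6, and 12 months after the traumatic injury". The Power analysis and sample size section recruits 200 "in order to retain 180 subjects at the 12-month post-injury follow-up". The Informed consent section describes payment for participation as running over the year following the injury.

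**No origin stated.** Table 1 has a baseline column followed by 3-, 6- and 12-month columns, without saying what those months are counted from.

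**Entry window.** The Eligibility criteria section admits adolescents with "at least three PCS that persist for at least 1 month but less than 9 months after injury".

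**School records.** The School performance section says that participants' "1 year pre- and post-injury school attendance and grades will also be obtained from school records". The Data analysis section compares GPA at 12 months with pre-injury GPA and does not say 12 months after what.

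**The concern.** The two clocks are not interchangeable. With the entry window as written, they differ by 1 to under 9 months for every participant. The Outcome evaluation rule covers everyone enrolled, yet an adolescent who enters more than 3 months after injury cannot supply a 3-month post-injury survey after randomization. That rule and the eligibility rule therefore cannot both be followed.

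The effect of major interest is the time-by-treatment interaction, so the time origin is part of the definition of what is tested. On an injury clock, time since injury and time since randomization would be mixed in that term.

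The school outcome is a second, separate problem. Its window is tied to injury by definition, so correcting the survey wording leaves it unchanged. Some of the outcome period precedes treatment assignment for everyone.

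**Working it through.** **1. The plan's own figures.** Inputs from the Power analysis section: 10% attrition, 180 retained (90 per arm), ρ = 0.7, four assessments, d = 0.36, two-sided α = 0.05.
- Recruitment: 180 / (1 − 0.10) = 200, as stated.
- Power for a difference averaged over four occasions: SD factor √[(1 + 3 × 0.7)/4] = √0.775 = 0.880, which gives 0.783 against the stated 0.80.
- Responder comparison, 44% against 65% with 90 per arm: 0.813 against the stated 0.80.

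None of these uses the time origin, so they stand whichever clock applies.

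**2. Where an injury-dated survey falls.** Let L be the months from injury to enrolment, 1 ≤ L < 9 (Eligibility criteria). A survey due f months after injury falls f − L months after enrolment.

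| Survey | Latest entry (L just under 9) | Earliest entry (L = 1) |
|---|---|---|
| f = 3 | almost 6 months before | 2 months after |
| f = 6 | almost 3 months before | 5 months after |
| f = 12 | just over 3 months after | 11 months after |

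The 12-month survey never precedes enrolment, but time since enrolment at that survey would vary more than threefold. On the baseline clock the surveys fall 4 to <12, 7 to <15 and 13 to <21 months after injury, and none precedes enrolment.

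**3. How many dates would already have passed at entry.** The article gives no distribution for L, so these are assumptions.
- Uniform on 1 to 9: share = (9 − f)/8.
- Early-skewed, exponential with scale θ truncated to 1–9: share = 1 − [1 − e^(−(f−1)/θ)] / [1 − e^(−8/θ)].

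| Assumption | 3-month date past | 6-month date past |
|---|---|---|
| θ = 1.5 months | 26% | 3% |
| θ = 3 months | 48% | 13% |
| θ = 6 months | 62% | 23% |
| Uniform | 75% | 37.5% |

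**4. Which clock the rest of the article fits.**
- The Data analysis section speaks of a year of participation. On the injury clock, participation would last just over 3 to 11 months.
- The Power analysis section lists the four assessments in the order baseline, 3, 6, 12 months. That order fails on the injury clock for anyone entering after month 3.
- The satisfaction questionnaire at 6 months asks about care received during the study, which presupposes time in the study.
- Trial status expects the full sample near the end of March 2019, and then: "The 12-month follow-up assessments of all the participants would then be completed by March, 2020". That is the 12-month gap of the baseline clock. On the injury clock the last survey would be due no later than about the end of February 2020, so this item taken alone is a pointer more than a proof.

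**5. School-record window.** The pre-randomization part of the one-year post-injury record is L/12, from 1/12 = 8% to just under 9/12 = 75%, for every participant. The post-randomization part is (12 − L)/12, from 92% down to just over 25%. The GPA comparison does not settle the matter. If 12 months means after baseline, the point lies 13 to <21 months after injury, outside the record window. If it means after injury, it includes time before treatment assignment.

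**The case against.** The strongest reply is that the article largely answers the survey question itself. The abstract, the Design section, the order of assessments and the calendar all point to baseline, so the injury wording can be read as loose drafting for a schedule nobody would run. Much of this stands. A reader might infer that up to three quarters of the 3-month surveys will be lost or taken before randomization, or that the primary comparison is confounded. The documents do not support that. Nothing shows surveys being scheduled from injury, and the 75% figure rests on the uniform lag, the highest of the assumptions tried. What does not fall away is that the section instructing data collection states a rule that conflicts with the eligibility criteria, and that two other sections repeat its origin. Condensing a protocol into an article explains missing detail, but not two incompatible origins.

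On the school records, it is fair to say that pre-injury grades must be anchored to injury, that a window symmetric about injury is natural, and that pre-randomization months affect both arms alike. This is therefore dilution and not bias. School performance is also a secondary outcome, and parents report on it at every follow-up.

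A reader might also want to express the dilution as lost power, for example by scaling d = 0.36 by the uniform-lag mean share of 7/12 to 0.21, which takes power from 0.78 to 0.36. That calculation is not supported. The effect size belongs to the HBI, the variance is a four-occasion average whereas Table 1 has school records at two points, and the scaling assumes an outcome averaged over the whole year with a constant effect from the day of randomization. The article gives no effect size for GPA or attendance.

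**Conclusion.** The concern holds in two parts.

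**Surveys.** The article gives two incompatible origins for the primary-outcome schedule. The injury-based rule in Outcome evaluation, echoed in Informed consent and Power analysis, is the wrong one on the evidence of the rest of the text. Followed literally, it would place about 26% to 75% of 3-month dates and 3% to 38% of 6-month dates before entry. The ranges run from the early-skewed to the uniform assumptions about a lag that the documents do not report. The 12-month survey would always follow entry, at just over 3 to 11 months. Stated sample size and power are unaffected.

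**School records.** For every participant, 8% to under 75% of the post-injury year precedes randomization. This follows from the entry window and needs no distributional assumption. It weakens the contrast for the third aim without favouring either arm. The loss of power cannot be quantified from the documents.

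The arithmetic treats enrolment, baseline and randomization as close together. The section on masking of treatment allocation places randomization after the baseline assessments without giving the interval.

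**What to change.** **Surveys.** Use the baseline date as the single origin. Change the injury wording in Informed consent, Outcome evaluation, and Power analysis and sample size to match the abstract and Design section, and state the origin in Table 1. Confirm that surveys are in fact scheduled from the baseline date. The cost is wording and one check of the scheduling rule.

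**School records.** Keep the pre-injury year as the reference and covariate. Define the post-treatment GPA and attendance outcome over the period from randomization to 12 months after it, and state in the Data analysis section that GPA at 12 months means 12 months after baseline. Table 1 already has a school-record collection at 12 months, so mainly the extraction window changes. The costs are a slightly later records pull, a check that the parental release covers the later terms, and a number of usable terms that varies somewhat with enrolment date.

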### Randomization

Randomization will occur in a 1:1 ratio, in blocks of four to six patients, according to a computer-generated random assignment sequence prepared by the study biostatistician. Once generated, intervention and control group assignments will be entered into a password-protected tracking system with access limited to study coordinator, care manager, and principal investigator. Randomization will be conducted by the study coordinator. After randomization occurs a letter and email will be sent to the referring provider and participant family to notify them as to which group the participant has been randomly assigned.

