#### Other outcome measures

##### Client Satisfaction Questionnaire

The eight-item Client Satisfaction Questionnaire will be used at 6 months to measure adolescent and parent satisfaction with services; it has excellent correlation with changes in symptom score [75]. An open-ended question was added to the end of the client satisfaction questionnaire, “*Please let us know if you have any other thoughts or additional comments about your experience with the care you received during the study*,” to allow participants to share their experiences of the intervention or of the usual care received.

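### Research assistants who are meant to stay blinded are trained in a retention conversation that is triggered by control-group status

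*Protocol article*

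**What the plan says.** Three sections of the protocol article bear on this point.

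- **Outcome evaluation.** Training teaches the research assistants to "bring up specific discussion points about the benefits of study participation in cases where control group families are unsure" whether to stay in the trial. The stated purpose is "to increase their retention and counteract differential dropout". The section gives no matching instruction for unsure intervention families. It does offer payment for each survey to all adolescents, and it invites those who left or only partly engaged with the intervention to keep answering surveys. Surveys are completed online or by telephone.
- **Masking of treatment allocation.** The assistants who conduct all baseline and follow-up interviews "remain blinded to study group assignment throughout the study". The section lists the principal investigators, study coordinator and care managers as unblinded and the research assistants as blinded. It adds that "unblinding of the research assistants is not ever necessary, although it could inadvertently occur through participant disclosure".
- **Randomization.** Assignments are held in a "password-protected tracking system with access limited to study coordinator, care manager, and principal investigator". Research assistants are not on that list. Families are told their own assignment by letter and email.

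**The concern.** An instruction whose trigger is control-group membership has been given to the one staff group that is supposed not to know group membership. Two things are at stake.

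The first is assessor masking. The primary outcomes (HBI, PHQ-9 and the anxiety scales) are adolescent or parent reports and may be taken by telephone. Families know their arm, so the research assistants are the only blinded staff group that the masking section names. A procedure that leads them to the arm weakens that safeguard.

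The second is equal retention effort. If extra persuasion is used in one arm, it can change which families remain in that arm as well as how many. The main analysis relies on data being missing at random, so the composition of the retained control group matters.

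**Working it through.** The question is procedural, so the check is mainly a comparison of the sections.

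**Step 1: can the instruction be followed by a blinded assistant?** There are three ways an assistant could act on it.

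1. The assistant is told the arm or looks it up. This contradicts both the masking section and the access list under Randomization.
2. The family reveals its arm while voicing doubt. No access to the list is needed, but the assistant is then unblinded. The masking section treats such disclosure as an accident, whereas Outcome evaluation makes a trained procedure depend on it.
3. The assistant does not know the arm and uses the talking points with any unsure family. Masking is preserved, but this is not the instruction as written.

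On each route, at least one section does not describe what happens.

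**Step 2: who is affected?** The instruction reaches control families who express doubt. A family that leaves anyway gives no later outcome data that an unmasked interviewer could influence. The group that matters is therefore control families who waver, have the conversation and stay.

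**Step 3: can that group be counted?** The inputs are in Power analysis and sample size: 200 recruited, 100 per group, 10% attrition at 12 months, 180 retained.

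- The plan's own figure reproduces: 180 / (1 − 0.10) = 200.
- If attrition were equal in the two arms (an assumption), expected control dropouts are 100 × 0.10 = 10.

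Those 10 are families who leave, some perhaps by not responding and so without any conversation. The figure neither counts nor bounds the families who waver and stay, and the document gives no number for them.

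**Step 4: is this a sample-size problem?** The plan states power of 0.80 for 44% against 65% still symptomatic at 12 months. With n = 90 per arm and two-sided alpha 0.05:

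- mean proportion = (0.44 + 0.65) / 2 = 0.545
- standard error under the null = √(2 × 0.545 × 0.455 / 90) = 0.0742
- standard error under the alternative = √((0.44 × 0.56 + 0.65 × 0.35) / 90) = 0.0726
- z = (0.21 − 1.96 × 0.0742) / 0.0726 = 0.89, giving power 0.813

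Holding 180 completers but splitting them unevenly (assumed splits, intervention/control) gives 0.812 for 85/95 and 0.809 for 80/100. Unequal retention of this order hardly changes power. The issue is masking and who is retained.

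**Step 5: does one-sided retention break missing at random?** Not by itself. Under MAR, dropout may depend on arm and on observed outcomes, and arm is in the model. MAR would fail only if, given the observed data, remaining in the study depended on unobserved outcomes, for example if persuasion worked better or worse according to current unrecorded symptoms. The document neither shows nor excludes this.

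**The case against.** The strongest defence is that the step is reactive. Families know their arm, and a disappointed control family may well say so. The masking section openly admits disclosure as a route, and nothing says that assistants are given assignments in advance. This stands in part: the text does not show planned access to the assignment list. It does not remove the conflict, because a procedure in which staff are trained cannot rest on an event that another section calls inadvertent.

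A second defence is that the text never says the talking points are withheld from intervention families, and a condensed article may omit a parallel script. That is fair, and the conclusion is limited to what is written. But the article names control families alone and gives retaining them as the aim.

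A third is that the effect is limited. The scales have fixed items, may be completed online, and come from respondents who are unblinded by design. The telephone share is not given. The analysis plan models attrition with treatment group among the predictors, adds explanatory factors as covariates and promises a non-MAR sensitivity analysis. The DSMB reviews differential dropout. All of this stands and limits the consequence, though it leaves the contradiction in place.

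A reader might also see a second leak in the 6-month satisfaction questionnaire, whose open question invites "additional comments about your experience with the care you received during the study". The answers could reveal the arm. However, the article does not say that research assistants collect or see them, so no leak to the assessors can be inferred.

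**Conclusion.** The contradiction between Outcome evaluation and Masking of treatment allocation is real and follows from the text alone. The instruction can be followed as written only if the assistant knows or learns the arm. It compromises assessor masking for wavering control families who stay, and it describes this retention effort for one arm only.

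Neither the number of families nor the size of any bias can be derived from the document. Three stronger readings go beyond it:

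- That masking fails for all 100 control participants at all three follow-ups. The trigger is expressed doubt, so only wavering families are reached.
- That at least 10 control families would be affected. Ten is expected dropout under equal attrition, not a lower bound on families who have the conversation.
- That missing at random is violated. This is a risk that depends on unobserved symptoms, and a non-MAR sensitivity analysis is already planned.

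The conclusion assumes that the research assistants in the two sections are the same staff. The article supports this by assigning all baseline and follow-up interviews to them and naming no other group of assistants.

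**What to change.** Reconcile the two sections in one of two ways.

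1. Give the same retention talking points to any family that is unsure about continuing, whatever its arm. Assistants then need no knowledge of assignment, and retention effort is equal by design.
2. If an arm-specific conversation is wanted, have research assistants pass every unsure family to the study coordinator, who is already unblinded, and let the coordinator hold it.

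The first is simpler and also removes the one-sided effort. The second protects masking but leaves retention effort different by arm. Both keep the legitimate aim of limiting dropout.

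The cost is a revised script, a short staff instruction and a few more minutes of existing staff time. Under Trial status, 12-month assessments were expected to run to March 2020 under a protocol version dated October 2018, so on that timetable a change could still protect later assessments.
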